### Sample/randomization and data-management

The literature highlights that up to 40 % of PWS disorders have a mean CPI ≥ 3 [27, 28], compared with less than 10 % in general population [24, 25]. Anticipating that the TEPOH will lead to a mean 20 % reduction in the CPI index of patients, taking into account cluster variability (CV = 0.37) and the intra-class correlation coefficient (CCI = 0.01), we will have to recruit a total of 202 patients to highlight a statistically significant difference between the two groups with a type-I error of 5 % and type-II error of 20 %.

Randomization will be done using SAS version 9.3 (SAS Institute Inc) by the team of statisticians of the Methodological Support Unit, Direction of Clinical Research, UHD, France. All participating hospitals will be randomly allocated to TEPOH or not using a random stratified sampling method depending on their location (urban/mixed/extra-urban) and their level of activity (number of patients per year). All data of included persons will be collected in an electronic case report form (CRF), created with the software CleanWeb™. Real-time likelihood and coherency tests will be implemented to check data entry with predefined rules in collaboration with all the co-investigators. Periodically, coherence reports will be sent to investigators with the aim to correct any highlighted errors. The database will be frozen only when all of the errors have been corrected and when no more are found.

### Statistical analysis

The interview data will be transcribed and coded using NVivo software to facilitate analysis of the factors identified by participants as affecting their attitudes and behaviours relating to changes in perception in OHRQoL. This process will yield a comprehensive account of the relevant barriers, motivators, and facilitators of OHRQoL. Among the intervention group participants, changes in attitudes will be documented. Results for qualitative covariates will be expressed as proportions. Quantitative variables will be expressed as means ± standard deviations (SD) when normally distributed, or as medians and ranges in other cases. Comparison of persons’ characteristics between a group of interest and the general population of PWS will be performed using Student’s *t* test, analysis of variance, Kruskal–Wallis non-parametric tests and Pearson’s Chi square or Fisher’s exact test when appropriate. A value of p < 0.05 will be considered statistically significant. All analyses will be performed using SAS version 9.3 (SAS Institute INC.).

Electronic data will be stored on secure data servers and hard copy materials will be retained in locked filing cabinets of Dijon University Hospital.

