**Methods/design:**

We report the protocol of a randomized controlled cluster study. This study will be conducted in twelve hospitals in France. We hypothesized that a decrease of 20 % in the proportion of patients with CPI ≥ 3 would establish the effectiveness of TEPOH. Therefore, 12 hospitals will be randomly allocated to either TEPOH or no TEPOH. Altogether, they will have to recruit 230 PWS, who will be randomly allocated with a ratio of 1:1 to one of two conditions: control without intervention versus the group benefitting from TEPOH.

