## Methods/design

It is a multicentre, cluster randomized controlled trial designed to assess the effectiveness of a TEPOH on PWS. Therefore, 12 hospitals will be randomly allocated to four clusters (a cluster is composed of three hospitals) where benefiting from TEPOH is available or not, and 230 PWS will be recruited and randomly allocated with a ratio of 1:1 to one of two conditions: control without intervention versus the group benefitting from TEPOH.

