#### Procedure

*In the first phase*, hospitals will be randomized and groups of five or six participants will be organized. Randomization will be collective between the hospitals and not between patients. The local catchment areas of the 12 psychiatric hospitals are sufficiently distant from each other to avoid a bias of contamination between individuals of the same hospital. The trial will be conducted in the open because it is not possible to assess a person’s oral health without the person and the operator knowing. Cluster randomization is recommended by the “la Haute Autorité de Santé” (HAS) in France for evaluation trials of interventions to improve practices.

*In the second phase*, patients able to participate in the study will be screened in each local catchment area. Consenting participants will be contacted to arrange an oral health assessment. Evaluations will be conducted at the outpatient unit or at the hospitals where the patients are followed. Prior to arriving in their TEPOH group, they will be asked to complete a battery of psychological and OHRQoL questionnaires. Participants’ socio-economic status (SES) will also be collected.

*In the third phase*, participants will undergo a battery of tests to assess their oral health disorders using clinical and radiological examinations. At the end of this step, the TEPOH will be performed or not depending on the cluster to which the PWS belongs.

Before the start of the TEPOH, the teams of caregivers for the patients will be invited to participate in a focus group interview to assess their knowledge of oral health and their practices in the management in OHrQOL with PWS.

*The fourth phase* will consist of an evaluation at 3 months, 6 months and at 1 year after the initiation of TEPOH. All participants (patients and caregivers) will be asked to complete the same battery of tests they completed at baseline except for radiological examinations and SES.

The interviews for the OHRQoL will be managed to ensure that participants in the two groups (control vs TEPOH group) do not interact with each other.

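### The only quantitative tests the protocol names ignore hospital clustering and are tied to a comparator the trial does not recruit, in conflict with its own cluster design

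*Protocol article*

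**What the plan says.** **Unit of randomisation.** The Procedure section of the protocol article is explicit: "Randomization will be collective between the hospitals and not between patients". The abstract agrees that "12 hospitals will be randomly allocated to either TEPOH or no TEPOH".

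**Contrast of interest.** Methods/design gives it as "control without intervention versus the group benefitting from TEPOH". Recruitment procedures tells participants that outcomes will be compared between intervention and control groups. The sample-size paragraph refers to a difference between the two groups.

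**Sample size.** Under Sample/randomization and data-management, 202 patients are required, "taking into account cluster variability (CV = 0.37) and the intra-class correlation coefficient (CCI = 0.01", and "with a type-I error of 5 % and type-II error of 20" per cent. Methods/design plans to recruit 230.

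**Analysis.** After sentences on qualitative interview coding and on summarising variables, the Statistical analysis section says that persons' characteristics will be compared "between a group of interest and the general population of PWS will be performed using" several standard tests. Besides the t test, it lists "analysis of variance, Kruskal–Wallis non-parametric tests and Pearson’s Chi square or Fisher’s exact test when appropriate". A p-value below 0.05 "will be considered statistically significant". The section names no other quantitative test, does not mention hospital as a factor, and does not tie any test to CPI ≥ 3 or to TEPOH against control.

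**The concern.** Two features of the stated analysis do not fit the design.

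- **Comparator.** The trial enrols TEPOH patients and control patients only. No section describes a separate sample of persons with schizophrenia in general, so the comparison named cannot be carried out on the trial's data as worded.
- **Class of test.** Each listed test, in its usual form, assumes that patients are independent. Patients within a hospital share staff, local care and the allocated condition, and the sponsor's non-zero ICC acknowledges this.

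If an analyst applied the listed tests to the two arms, the standard error would be too small, the intervals too narrow and the error rate above the planned 5%. The clustering allowance built into recruitment would not be carried through to the test.

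**Working it through.** **1. Reproduce the plan's sample size.** Inputs: control proportion with CPI ≥ 3 of 40% (Background; sample-size paragraph), effect 20% (abstract), two-sided alpha 5%, power 80%, ICC 0.01, CV 0.37. Three readings are assumed: the effect is 20 percentage points (40% to 20%), CV is the coefficient of variation of cluster size, and alpha is two-sided.

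- Two proportions, pooled formula: n per arm = [1.96·√(2·0.3·0.7) + 0.842·√(0.4·0.6 + 0.2·0.8)]² / 0.2², which rounds up to 82, or 164 in total.
- Design effect: DE = 1 + ((1 + CV²)·m − 1)·ICC.
- With m = 230/12 = 19.2: DE = 1 + (1.1369·19.17 − 1)·0.01 = 1.208, and 164·1.208 rounds up to 199. With m = 20 the result is 200.

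This is close to the stated 202. A relative reduction (40% to 32%) would need at least 1,333 patients. The stated size is therefore consistent with a design effect of about 1.2, against 164 patients without one.

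**2. Type I error if the listed tests are used on the arms.** An unadjusted test has true two-sided error 2·(1 − Φ(1.96/√DE)).

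| ICC | DE, N = 202 (m = 16.8) | Error | DE, N = 230 (m = 19.2) | Error |
|---|---|---|---|---|
| 0.01 (plan) | 1.181 | 0.0714 | 1.208 | 0.0745 |
| 0.02 (assumed) | 1.363 | 0.0932 | 1.416 | 0.0995 |
| 0.05 (assumed) | 1.907 | 0.1558 | 2.040 | 0.1699 |

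At ICC 0.01 the standard error is understated by 8% (1 − 1/√1.181) to 9% (1 − 1/√1.208).

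**3. Check by simulation.** Setting: beta-binomial data, 40% base rate, 12 hospitals of unequal size, six per arm, patient-level chi-square, 40,000 runs per setting. Rejection rates at N = 202 and N = 230 were 7.5% and 7.4% at ICC 0.01, 9.2% and 10.1% at 0.02, and 15.4% and 17.0% at 0.05. With the ICC near zero they were 5.1% and 5.0%. In a separate simulation at N = 202, a t test on the 12 hospital proportions stayed at about 5% at both ICC 0.01 and 0.05.

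**4. Power of a clustered analysis at ICC 0.01, 40% against 20%.** SE = √[(0.24 + 0.16)/(N/2/DE)].

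- N = 202: SE = √(0.40/85.5) = 0.068. Power is 0.82 by normal approximation and 0.75 with a t reference on 10 df.
- N = 230: SE = √(0.40/95.2) = 0.065. Power is 0.86 by normal approximation and 0.79 on 10 df.

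**The case against.** The strongest reply is that the sentence concerns persons' characteristics and follows text on summarising covariates. It does not mention CPI, TEPOH, control or any visit. It may be purely descriptive, with the outcome model left to a fuller document. An article may properly leave that out, and silence about a model is not the point here.

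That reply removes part of the case. A reader might infer that the trial will not test TEPOH against control. The documents do not support this: Methods/design, Recruitment procedures and the sample-size paragraph all state that contrast, and the sponsor plainly knew of the clustering. The error-rate calculation is also conditional, because the article never expressly assigns the listed tests to the arms.

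What stands is the conflict in what is written. Even as description, the named comparator is not part of the trial. The section attaches its significance threshold to a list of independent-patient tests and to nothing else. A reader following the article would have only those tests to apply.

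One might also point out that Methods/design describes patients as allocated 1:1, which would suit independent-patient tests. The Procedure section rules out patient-level randomisation.

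**Conclusion.** The point holds as a conflict between the stated analysis and the stated design. The aim of the trial is not in doubt. If the listed tests are used for the arm comparison, the two-sided error is about 7.1% to 7.5% at the plan's own ICC. That is a modest but real departure from 5%.

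A reader might take the larger figures, about 9–10% at ICC 0.02 and 16–17% at 0.05, as the expected error. They are not: those ICCs do not appear in the document and only show how fast the error grows if 0.01 proves too low.

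The figures assume 12 independently randomised hospitals, CV as variation in cluster size and a two-sided test. The power figures also assume 40% against 20%. Methods/design instead speaks of four clusters of three hospitals. If those four are the randomised units, the figures above do not apply, and an unpaired cluster-level t test would have 4 − 2 = 2 degrees of freedom rather than 12 − 2 = 10.

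**What to change.** First reconcile the 12 hospitals with the four clusters of three in Methods/design, and state which unit is randomised. This sets the degrees of freedom.

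Then replace the comparison sentence in Statistical analysis with text to this effect: the primary analysis compares the proportion of patients with CPI ≥ 3 between TEPOH and control, each patient being analysed in the arm of their hospital. It uses a mixed logistic model with a random effect for the randomised unit and a small-sample correction, or a cluster-level test (10 df if 12 hospitals are randomised). Stratification by location and activity is taken into account where the number of units allows. Secondary outcomes are handled with the same regard for clustering. The tests now listed are kept for description only, and the reference to a wider population of persons with schizophrenia is removed or explained.

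The cost is mainly wording. No new patients or data are needed, and the Trial status section places cluster randomisation and first inclusions in the future. Intervals will be wider. Power on 10 df is about 0.75 at 202 patients or 0.79 at 230, rather than 0.80, and the protocol should say so. Adjusting a hospital-level analysis for the three location categories would use two of the ten degrees of freedom, which these power figures do not include.

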## Discussion

### Innovation

This document provides a complete description of the construction, the use and evaluation of the effectiveness of TEPOH specifically designed for PWS with their active participation for the first time.

The current study is innovative because it proposes to investigate the impact of a strong partnership between PWS and their caregivers to improve their oral health in France.

This TEPOH can be used to promote OHRQoL in a global health approach and to develop appropriate strategies to encourage and facilitate financial support for healthcare, the multidisciplinary treatment of dental disorders, prospective support for patients, and the development of training in oral or mental health for caregivers.

## Limitations

The active participation of patients is a key component of the study. However, the major difficulties with the inclusion of PWS in a long-term protocol study is that many PWS may be unable to cooperate due to their psychiatric illness, or lost to follow-up, or die during the study.

Secondly, although oral health has an impact on general health, self-esteem and quality of life often have a low priority in persons with psychiatric diseases in France. Furthermore, the somatic care of patients undergoing psychiatric treatment remains heterogeneous.

In this case, a key component will be the participation and involvement of healthcare teams in introducing TEPOH in their practices and in promoting TEPOH in all units of the hospital.

### Impact

Finally, this study is needed to inform the development of public policy and interventions that have the potential to improve the OHRQoL of PWS and the feasibility to engage PWS as full partners in TEPOH.

## Trial status

The preliminary phase of the study is completed and data collection for patients is closed. We will proceed with randomization of the clusters and will include the first patients in the study during July, 2016.

## Abbreviations

PWS: persons with schizophrenia
WHO: World Health Organization
TE: therapeutic educational
TEC: therapeutic educational concept
OHRQoL: oral health quality of life
FGAs: first-generation antipsychotics
SGAs: second-generation antipsychotics
TEPOH: therapeutic education program in oral health
CPP: committee for the protection of persons
FG: focus group technique
IREPS: Instance Régionale d’Education et de Promotion de la Santé”
DSM-5: Diagnostic and Statistical Manual of Mental Disorders-Fifth edition
CRF: case report form
HAS: Haute Autorité de Santé
GOHAI: global oral health assessment index
CV: cluster variability
ICC: intra class correlation
S-QOL: schizophrenia quality of life questionnaire
BDI-II: Beck Depression Inventory-II
DMFT: decayed missing filled teeth
SES: socio-economic status
OHI-S: simplified oral hygiene index
CPITN: community periodontal index of treatment needs
REC: Research Ethics Committee
PANSS: positive and negative syndrome scale
SD: standard deviation
